### 10.1.3 Follow up of Serious Adverse Events

SAE will be reported from the moment starting the intervention until the end of the study to EC according to Swiss regulations. Participants terminating the study (either regularly or prematurely) with reported ongoing SAE, or vital signs being beyond the limit will be followed up until the end of the study (60 days after the administration of the first dose of the vaccine).

All SAE are collected, fully investigated and documented in the source document and appropriate CRF during the entire study period, i.e. from patient's informed consent until the last protocol-specific procedure, including a safety follow-up period. Documentation includes dates of event, treatment, resolution, assessment of seriousness and causal relationship to device and/or study procedure.

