## **6. STUDY DESIGN**

### **6.1 General study design and justification of design**

This is an open, monocentric, controlled, randomized clinical study conducted with healthy volunteers to evaluate anti-*Salmonella* porins specific immune responses after vaccination with the commercial live attenuated *Salmonella* vaccine Vivotif®. 15 subjects will be vaccinated with Vivotif® and 5 subjects will be left untreated. The study will consist of 7 visits that in total will last 67 days. For a general description of the times in which every assessment will be performed please refer to table 1 in section 9.1. For a description of the procedures performed in the different phases of the study please refer to section 9.3.

The results obtained from this study will reflect the specific cellular and humoral immune responses against *Salmonella Typhi* porins induced during vaccination. The study was designed to have the minimum number of visits possible to increase the probability of study completion by the participants. Enough time of follow up after vaccination is given to analyse the specific anti-porins immune responses in a timeframe that allows collecting solid data.

From the screening of the first participant to the end of follow up, the study will last approximately 3 months. The first participant-in is expected to be in June, 2015 and the last participant-out is expected for September, 2015. End of trial is expected by November, 2015.

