## **8.5 Data Collection and Follow-up for withdrawn participants**

If a subject withdraws during the interventional phase of the study and does not consent to continued follow-up of associated clinical outcome information, the investigator will not access, for purposes related to the study, the subject's medical record or other confidential records requiring the subject's consent.

If a subject withdraws during the interventional phase of the study but agrees to continue with the follow up of associated clinical outcome information, the following measures for data collection will be taken depending on the time point of withdrawal: a) Data from anti-porins specific immune responses will only be included in the analysis when the participant withdraws after visit 5, and b) Data from study subjects withdrawn at early time points will only be used for the genetic analysis of live attenuated bacteria contained in the formulation (applicable for study subjects that withdraw after visit 3).

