### **9.3.7 Visit 7. Follow-up visit, day 60.**

Measurement of vital signs

Blood sample collection for evaluation of specific anti-porins immune responses (day 56 after last immunization)

Stool sample collection for determination of IgA antibodies (day 56 after last immunization)

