#### 10.1.1 Definition and assessment of (serious) adverse events and other safety related events

An **Adverse Event** is any untoward medical occurrence in a patient or a clinical investigation participant administered a pharmaceutical product and which does not necessarily have a causal relationship with the study procedure. An AE can therefore be any unfavourable and unintended sign (including an abnormal laboratory finding), symptom, or disease temporally associated with the use of a medicinal (investigational) product, whether or not related to the medicinal (investigational) product. [ICH E6 1.2]

A **Serious Adverse Event** is classified as any untoward medical occurrence that:

- results in death,
- is life-threatening,
- requires in-patient hospitalization or prolongation of existing hospitalisation,
- results in persistent or significant disability/incapacity, or
- is a congenital anomaly/birth defect.

In addition, important medical events that may not be immediately life-threatening or result in death, or require hospitalisation, but may jeopardise the patient or may require intervention to prevent one of the other outcomes listed above should also usually be considered serious. [ICH E2A]

SAEs should be followed until resolution or stabilisation. Participants with ongoing SAEs at study termination (including safety visit) will be further followed up until recovery or until stabilisation of the disease after termination.

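### Section 10.1.3 stops follow-up of ongoing SAEs at day 60, while section 10.1.1 requires it to continue after study termination until recovery or stabilisation

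*Protocol*

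**What the plan says.** Two parts of the protocol's safety chapter say how long an SAE is followed.

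- **Section 10.1.1** gives a general rule, "SAEs should be followed until resolution or stabilisation", and then deals with events that outlast the study. "Participants with ongoing SAEs at study termination (including safety visit") "will be further followed up until recovery or until stabilisation of the disease after termination". It sets no calendar limit.
- **Section 10.1.3**, the section devoted to SAE follow-up, covers "Participants terminating the study (either regularly or prematurely) with reported ongoing SAE", together with those whose vital signs are out of range. It says they "will be followed up until the end of the study (60 days after the administration of the first dose of the vaccine"). This is a fixed calendar stop.

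The calendar comes from three other places. Section 9.3.7 is headed "Visit 7. Follow-up visit, day 60", and the schedule tables give that visit as day 60 ± 1. Section 9.3.2 puts the first dose at day 0. Section 6.1 states: "The study will consist of 7 visits that in total will last 67 days".

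**The concern.** Section 10.1.3 names completers as well as early leavers, so a participant who attends every visit and still has an unresolved SAE falls under both rules. Section 10.1.1 tells staff to carry on after termination; section 10.1.3 tells them that follow-up runs to day 60. Neither section refers to the other.

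What is at stake is the care and documentation of a participant with an unresolved serious event. Staff who look up the section titled for SAE follow-up and apply it literally would stop at about Visit 7 and so breach 10.1.1. Staff who apply 10.1.1 would go past the end point in 10.1.3. SAEs are the only adverse events this protocol collects (section 10.1), so their follow-up rule should be unambiguous. The immune-response and bacterial-mutation analyses do not depend on it.

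**Working it through.** **Inputs**

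| Input | Value | Source |
|---|---|---|
| First dose | day 0 | 9.3.2 |
| Third dose | day 4 | 8.2.1 and schedule tables |
| Visit 6 | day 25 ± 1 | schedule tables |
| Visit 7, last scheduled visit | day 60 ± 1 | 9.3.7 and schedule tables |
| Earliest screening day | day −7 | schedule tables |
| End of SAE follow-up, rule A | 60 days after first dose | 10.1.3 |
| End of SAE follow-up, rule B | recovery or stabilisation, after termination | 10.1.1 |

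**Step 1. Is day 60 the end of the scheduled study?** Visit 7 is 56 days after the last dose, and 4 + 56 = day 60. The total length in section 6.1 is reproduced by 7 screening days + 60 = 67 days. No visit is scheduled later.

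**Step 2. Follow-up left for a completer after Visit 7 under rule A** (60 − day of Visit 7):

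- Visit 7 on day 59: 60 − 59 = 1 day
- Visit 7 on day 60: 60 − 60 = 0 days
- Visit 7 on day 61: the limit has already passed

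Under rule B the same participant is followed for as long as the event needs.

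**Step 3. When do the two rules give different results?** Only when the SAE is still unresolved and not stabilised at day 60, that is, when its duration exceeds 60 − onset day:

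| Onset | Calculation | The rules differ if the SAE lasts more than |
|---|---|---|
| Day 4 (third dose) | 60 − 4 | 56 days |
| Day 25 (Visit 6) | 60 − 25 | 35 days |
| Day 53 | 60 − 53 | 7 days |

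The onset days are illustrations. The protocol gives no SAE rate, so no expected number of affected participants can be calculated.

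**Step 4. Does other text settle which rule holds?**

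- Section 8.3 says treatment after an SAE continues until the participant has fully recovered, with no day limit. It agrees with 10.1.1, but it is a rule about treatment and does not say which follow-up rule prevails.
- Sections 10.1 and 10.1.3 mention a safety follow-up period, and 10.1.1 mentions a safety visit. None of these is given a date or length, and no visit after day 60 is scheduled, so they do not extend the limit in 10.1.3.

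**The case against.** The best defence is to read the two sections in sequence. Section 10.1.3 says follow-up runs until day 60; it does not say it then ceases. On this reading it guarantees follow-up to day 60, including for those who leave early, and 10.1.1 takes over after termination. Its wording about following participants further suggests a continuation. Section 8.3 points the same way, so a careful investigator would probably not abandon anyone at day 60.

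This reading works for early leavers but not for completers. A guarantee to day 60 adds essentially nothing for someone whose last visit is on day 60, yet 10.1.3 names completers explicitly. It also gives day 60 as an end point, not a minimum, and does not refer to 10.1.1.

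The second objection is about size: a licensed vaccine at its licensed dose, 15 vaccinated and 5 untreated volunteers, no safety objective or safety analysis, and no effect on any result. That is correct, and it limits the importance of the point. It does not make the two rules compatible. That staff would in fact stop at day 60 is a possibility, not something the text can show.

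A third objection is that the consent condition in section 8.5 concerns people who withdraw during the interventional phase, so it should not be attached to completers. That is a fair point about drafting, and the change proposed here keeps the condition to the people it already covers.

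**Conclusion.** The inconsistency is real. For a regular completer with an unresolved SAE, 10.1.3 allows between 0 and 1 day of follow-up after Visit 7, while 10.1.1 requires follow-up until recovery or stabilisation. Section 10.1.3 is the outlier, since 10.1.1 and 8.3 both point past day 60.

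The practical reach is small: only late-onset or long-lasting SAEs are affected, and in 20 healthy volunteers these are likely to be rare. That last judgement is an assumption, because the protocol gives no SAE rate. The conclusion also takes the words of 10.1.3 at face value and takes Visit 7 as the last contact, as the schedule shows. It should be corrected because it concerns participant safety and costs almost nothing to put right; no endpoint or analysis changes.

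**What to change.** In section 10.1.3, replace the day-60 limit for ongoing SAEs with the rule of section 10.1.1. For example:

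> An SAE that is unresolved when a participant completes or leaves the study is followed until it resolves or stabilises, beyond day 60 where necessary (see section 10.1.1). For participants who withdraw during the interventional phase and decline continued follow-up, sections 8.5 and 9.2.5 apply.

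The second sentence is needed because 8.5 bars access to the records of a participant who withdraws in that phase and "does not consent to continued follow-up of associated clinical outcome information". It places no condition on completers. The day-60 limit can stay for out-of-range vital signs if that is intended, but it should then be in a separate sentence.

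The cost is one sentence of protocol wording. No scheduled visit, sample or analysis is added; the only extra work is contact after Visit 7 for the occasional participant whose SAE has not resolved.

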## 10.2 Medical Device Category C studies

Not applicable.

### 10.2.1 Definition and Assessment of Serious Adverse Events and other safety related events

Not applicable.

### 10.2.2 Reporting of (Serious) Adverse Events and other safety related events

Not applicable.

### 10.2.3 Follow up of (Serious) Adverse Events

Not applicable.

## 10.3 Medical Device Category A studies

### 10.3.1 Definition and Assessment of safety related events

Not applicable

### 10.3.2 Reporting of Safety related events

Not applicable.

## **11. STATISTICAL METHODS**

### **11.1 Hypothesis**

Specific immune responses against porins are generated after the administration of Vivotif® to healthy volunteers.

$H_1$ : The median difference of specific immune responses after and before immunization is not zero.

$H_0$ : The median difference of specific immune responses after and before immunization is zero.

### **11.2 Determination of Sample Size**

This study is a pilot study; therefore, no sample size calculation was done. Fifteen participants in the Vivotif® group were considered sufficient to evaluate the methods and obtain meaningful results with respect to the induction of specific immune responses. Five untreated participants will serve as control.

### **11.3 Statistical criteria of termination of trial**

The investigator may withdraw a participant from the trial for the following reasons:

- violation of the criteria for inclusion and/or
- Non-compliance of the subject (cf. 8.4).

### **11.4 Planned Analyses**

#### **11.4.1 Datasets to be analysed, analysis populations**

In the experimental group, all subjects who received all three doses of vaccine will be included in the study analysis.

All subjects randomized to the control group will be included in the analysis.

#### **11.4.2 Primary Analysis**

The primary analysis of this study will focus on the determination of the antibody levels of IgM and IgG specific against porins in serum and stool, the number of porins-specific T cells from blood and the amount of porins-specific B cells in blood. Descriptive statistics will be shown separately for both treatment groups and will include the mean, sd, median, first and third quartile, minimum, and maximum for all time points. Differences to baseline will be investigated separately for both groups with a Wilcoxon signed rank test. If the distribution of the paired differences is not symmetric, the data may need to be transformed to produce symmetry.

#### **11.4.3 Secondary Analyses**

In the secondary analyses, the proportion of mutants from the original inoculum of live attenuated bacteria (Vivotif® vaccine) will be evaluated. The mean, sd, median, first and third quartile, minimum and maximum will be shown for all time points.

A Mann-Whitney  $U$  tests will be used to compare treated and untreated participants with respect to immune responses at baseline. Moreover, the mean immune response for visits 5-7 will be computed for each participant and compared between treated and untreated participants with a Mann-Whitney  $U$  test.

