#### **9.3.2 Visit 2. Intervention visit, day 0.**

Enrolment in the study of participants that fulfil eligibility criteria (refer to section 7.1)

Measurement of vital signs

Blood sample collection to be used as a control before vaccination for the evaluation of specific anti-porins immune responses.

Stool sample collection to be used as control for the evaluation of anti-porins immune responses (determination of specific IgA antibodies against *S. Typhi* porins) before the vaccine administration and as a control for the evaluation of genetic changes of live attenuated bacteria contained in the formulation.

Administration of first vaccine dose.

Reporting of SAE starts at this time point and lasts until the end of the study.

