### **11.5 Handling of missing data and drop-outs**

An available data analysis will be performed, thus, missing data will not be imputed. A common problem in clinical trials is the missing data that occurs when patients do not complete the study and drop out without further measurements. Missing data cause the usual statistical analysis of complete or all available data to be subject to bias. There are no universally applicable methods for handling missing data. In this study the following measures will be taken:

- (1) Reasons for dropouts and proportions for each treatment group will be reported. Characteristics for participants who did or did not drop-out of the study will be compared to determine if there are any clinically relevant differences between the two groups.
- (2) Careful conduction of the study will be made to minimize the chance of dropouts.
- (3) Post-dropout data will be collected on the primary endpoints, if at all possible.
- (4) Depending on the time frame of the study drop-outs could be replaced, with previous authorization from the investigator and the sponsor.

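### The only between-arm test of post-vaccination response ignores the visit 2 baseline: valid, but possibly inefficient at 15 v 5

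*Protocol*

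**What the plan says.** The trial is randomised and small: "15 subjects will be vaccinated with Vivotif® and 5 subjects will be left untreated" (Protocol 6.1). Section 9.2.1 has every immune endpoint measured once before vaccination, at visit 2, and three times after it, at visits 5, 6 and 7. Section 9.3.2 gives the purpose of the visit 2 sample: "Blood sample collection to be used as a control before vaccination for the evaluation of specific anti-porins immune responses".

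Baseline then appears in three places in section 11:

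- **Hypothesis (11.1).** The alternative is a before/after difference: "The median difference of specific immune responses after and before immunization is not zero". No between-arm hypothesis is stated.
- **Primary analysis (11.4.2).** "Differences to baseline will be investigated separately for both groups with a Wilcoxon signed rank test". This uses baseline fully, but only inside each arm.
- **Secondary analyses (11.4.3).** Mann-Whitney "tests will be used to compare treated and untreated participants with respect to immune responses at baseline". A second Mann-Whitney test then takes the post-vaccination data: "the mean immune response for visits 5-7 will be computed for each participant and compared between treated and untreated participants". Baseline plays no part in that second test.

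**The concern.** The second test in 11.4.3 is the only planned analysis that uses the randomisation to ask whether vaccination changed the response. With 5 controls it can spare little precision, yet it leaves out a measurement that is already collected and that the protocol treats as the reference point everywhere else.

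The chance difference in mean baseline between the arms has a standard error of √(1/15 + 1/5) = 0.52 SD. Under normality, a gap above 0.5 SD arises in about one trial in three, and on average a fraction r of that gap carries into the unadjusted comparison. Varied baselines are plausible: section 7.1 excludes oral *Salmonella* vaccination or *Salmonella* gastrointestinal infection only within the past 3 years, while section 3.2 describes efficacy lasting at least 5 years.

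The between-arm baseline test does not help. Under random allocation its null hypothesis is true by design, and 11.4.3 attaches no action to its result.

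**Working it through.** The protocol gives no significance level, power, effect size, SD or within-participant correlation for this comparison, so there is no planned figure to reproduce.

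**Inputs from the protocol:** 15 v 5 participants (6.1); one baseline and three post-vaccination visits (9.2.1); 5 endpoints (serum IgM, serum IgG, stool IgA, T cells, B cells), or 6 if CD4+ and CD8+ T cells are counted separately (5.1, 9.2.1).

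**Assumptions:** two-sided 5% level; SD 1 at each visit; the same correlation r between any two visits; complete data.

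**1. Variance of what is compared, per participant**

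- Raw mean of visits 5-7: (1 + 2r)/3
- Mean of visits 5-7 minus baseline: (1 + 2r)/3 + 1 − 2r = (4 − 4r)/3
- Mean of visits 5-7 adjusted for baseline: (1 + 2r)/3 − r²

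| r | Raw | Change | Adjusted | Cut by adjustment |
|---|---|---|---|---|
| 0.2 | 0.467 | 1.067 | 0.427 | 9% |
| 0.3 | 0.533 | 0.933 | 0.443 | 17% |
| 0.5 | 0.667 | 0.667 | 0.417 | 38% |
| 0.7 | 0.800 | 0.400 | 0.310 | 61% |

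Example at r = 0.7: 0.80 − 0.49 = 0.31, and 1 − 0.31/0.80 = 61%. A change score equals the raw mean when 4 − 4r = 1 + 2r, that is at r = 0.5. Below that it is worse than the planned analysis.

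**2. Simulated power, 1 SD effect, normal data, same effect in every vaccinee**

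| r | Mann-Whitney, raw (planned) | Mann-Whitney, change | Rank-based ANCOVA | Parametric ANCOVA |
|---|---|---|---|---|
| 0.3 | 64% | 42% | 72% | 75% |
| 0.5 | 54% | 55% | 74% | 79% |
| 0.7 | 47% | 76% | 80% | 89% |

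Not all of the gap to parametric ANCOVA comes from baseline. A t-test on the raw mean already reaches 71% at r = 0.3 and 54% at r = 0.7, so about 7 points come from leaving the exact rank test. The rank-based column is the fairer comparison with the plan.

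**3. If the vaccine effect itself varies between vaccinees (SD 1 around a mean of 1 SD)**

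Raw Mann-Whitney v parametric ANCOVA becomes 35% v 33% at r = 0.3, 32% v 35% at 0.5 and 29% v 37% at 0.7. Rank-based ANCOVA still gains, but only about 2 to 13 points.

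**4. Validity of the planned test**

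With no effect, the raw Mann-Whitney test rejected in 4.0 to 4.2% of simulated trials, as it should.

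**5. Baseline tests**

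The exact Mann-Whitney test at 15 v 5 has 15,504 arrangements. It rejects at U ≤ 14 or U ≥ 61, and its true size is 4.2% (0.0418). The chance of at least one significant baseline difference under correct randomisation, if the endpoints are independent, is 1 − (1 − 0.0418)⁵ = 19% for five and 1 − (1 − 0.0418)⁶ = 23% for six.

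**The case against.** The best defence is that this is a secondary analysis in a 20-person pilot without a power claim, that the test is valid as written, and that covariate adjustment is often left to a statistical analysis plan. The first two parts stand and limit the weight of the point. The third does not: 11.4.3 already names the summary, the comparison and the test, so an adjusted analysis would depart from the protocol.

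The size of the gain is also open. The correlation is not given and probably differs by endpoint; ELISpot or IFN-γ counts near zero at baseline would gain little. Section 3 of the working shows the gain shrinking when vaccinees respond unequally, with parametric ANCOVA no better than the plan at r = 0.3. This stands, and it is why a range is given and a rank-based version preferred.

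A reader might infer more than the protocol supports:

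- **That baseline is wasted altogether.** It is not: the hypothesis and the primary analysis are built on differences to baseline.
- **That the planned test is biased, or lets imbalance pass as a vaccine effect.** A misleading result from chance imbalance is part of the ordinary type I error, which the test controls.
- **That adjustment is worth several times the sample size.** This holds only at high r with a uniform vaccine effect.
- **That six baseline tests carry a 26% false-alarm risk.** That takes a size of exactly 5%; the exact test has 4.2%.
- **That missing visits spoil the visit 5-7 mean.** Section 11.5 says "An available data analysis will be performed, thus, missing data will not be imputed", so means could rest on different visits. How far this will happen is unknown, and the averaging rule may properly sit in an analysis plan that is not shown.

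**Conclusion.** The point holds as one of efficiency. The only between-arm test of post-vaccination response leaves out a baseline measured for every immune endpoint. Adjustment would lower the variance whenever baseline and later values are positively correlated: modestly at r of 0.2 to 0.3 and substantially from about 0.5. These figures assume equal correlation between visits, complete data and a uniform vaccine effect; the power figures also assume normality. The between-arm baseline tests add no usable information and carry a 19 to 23% chance of a spurious imbalance if the endpoints are independent. The change is worth making because it is nearly free and the control arm has 5 people, but the plan as written would not produce an invalid result.

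**What to change.** In 11.4.3:

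1. Replace the raw comparison by a baseline-adjusted one. Preferably, for each endpoint, rank the visit 5-7 mean and the visit 2 value over all participants, fit analysis of covariance of the response rank on arm and baseline rank, and take a permutation p-value that reassigns arm labels as the block randomisation did. Ranks cope with zero cell or spot counts, which a log model does not without an added rule.
2. Do not substitute a plain change score; it gains only when r exceeds about 0.5.
3. Delete the Mann-Whitney tests that "compare treated and untreated participants with respect to immune responses at baseline", and show baseline values descriptively by arm.

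The cost is one degree of freedom and slightly more analysis work. No new data are needed. Like the planned Mann-Whitney test, a rank-based analysis gives no effect size on the assay scale, so the descriptive summaries already planned in 11.4.2 should accompany it. Fix the wording before any post-vaccination data are examined.
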